#### Additional analyses

Exploratory endpoints, such as microbiota diversity, will be analyzed using multivariate methods (e.g., LEfSe, DESeq2).

#### Reference to statistical analysis plan

Further details on statistical procedures, variable definitions, and subgroup analyses are described in the Statistical Analysis Plan (SAP) maintained separately from the protocol. The SAP will be finalized prior to database lock and is available upon request.

### Interim analyses {21b}

No formal interim efficacy analyses are planned. However, interim safety monitoring will be conducted regularly to assess for any unexpected adverse events or safety concerns related to the study intervention (FMT or placebo).

Descriptive safety data (e.g., frequency and severity of adverse events, lab abnormalities) will be summarized after the first 5 and 10 participants have completed both treatment visits and at least one follow-up; this safety monitoring will focus on tolerability of FMT, consistency of laboratory findings, and any serious or unexpected adverse events.

#### Stopping guidelines

The study may be paused or terminated early based on the occurrence of unexpected serious adverse events (SAEs) potentially related to the intervention or emerging data from this or external studies that indicate unacceptable risk or lack of feasibility.

Stopping decisions will consider the nature, frequency, and severity of adverse events and the recommendations from the Data Safety Monitoring Committee (DSMC).

Only the DSMC and the sponsor investigator ([name]) will have access to cumulative interim safety data. The DSMC will review unblinded safety data and provide recommendations regarding study continuation, modification, or termination. Final decisions regarding early termination of the trial will rest with the sponsor investigator in consultation with the DSMC and REB, based on participant safety and scientific justification.

### Methods for additional analyses (e.g., subgroup analyses) {20b}

#### Subgroup analyses

Subgroup analyses will be exploratory and performed to assess whether the treatment effect varies by specific baseline characteristics. Potential subgroups include:CD4/CD8 ratio (e.g., ≤0.5 vs. >0.5)Age groups (e.g., <50 vs. ≥50 years)Sex at birthBaseline microbiota composition or diversity metricsPresence or absence of optional colon biopsy participation

Subgroup comparisons will use interaction terms in regression models or stratified analyses to explore differential responses to FMT vs. placebo. These analyses are hypothesis-generating and will be interpreted with caution due to limited power.

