### Sample size {14}

A total of 20 PWH participants will be enrolled, randomized 1:1 into two groups: FMT group (10 participants) and placebo group (10 participants).

The influence of gut microbiota targeting therapies on REG3α levels has not been tested yet. Hence, we calculated that based on the difference in REG3α levels between ART-treated (2441 ± 630 pg/mL) and HIV-negative controls (715 ± 243 pg/mL) [36], a sample size of 5 participants per group would allow 80% power to observe an effect, with a *p* value of 5% (https://clincalc.com/stats/samplesize.aspx). The clinical assumption and hypothesis is that complete change in the gut microbiota towards the one of HIV-negative controls would lower REG3α levels to those of controls. However, as previous FMT trials did not obtain 100% engraftment of the donor microbiota, sample size per group was doubled with 10 participants per arm. Due to the exploratory nature of the study, the small sample size is considered sufficient to detect preliminary signals in biomarkers of gut permeability, immune activation, and microbial translocation. Our study will inform larger, future randomized controlled trials as the variability in outcomes like REG3α, inflammatory markers, and microbiota composition will be estimated to support future power calculations.

As for the sub-study sample size, the optional colon biopsy sub-study includes a subset of the main study participants. No specific target number for this subgroup is defined, but participants must first qualify for and consent to the main study. In previous trials, around 50% of participants agreed to partake in the sub-study with colonoscopy as it can benefit participant with cancer screening [44–46].

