#### Secondary outcome analysis

Secondary outcomes include changes in inflammatory and gut permeability markers (e.g., I-FABP, LPS, cytokines), immune activation markers (e.g., HLA-DR, CD38 on T cells and CD83, CD86 on myeloid cells), and safety and tolerability outcomes (e.g., adverse events, hematology, HIV viral load).

These will be analyzed using repeated measures ANOVA or mixed-effects models to evaluate group-by-time interactions, non-parametric tests where assumptions are violated, and categorical variables (e.g., adverse event incidence) analyzed using chi-square or Fisher’s exact test.

All tests will be two-sided with a significance level set at *α* = 0.05.

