#### Statistical considerations

All additional analyses will be clearly labeled as exploratory. Results will be interpreted in the context of the small sample size and multiple comparisons and no formal correction for multiplicity will be applied in these exploratory analyses.

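### The subgroup plan lets stratified analyses replace the interaction term, so a differential response could be stated without any estimate of the difference between strata

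*Protocol article*

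**What the plan says.** Under Methods for additional analyses {20b}, Subgroup analyses, the protocol article says these analyses are "performed to assess whether the treatment effect varies by specific baseline characteristics". It lists five potential factors: CD4/CD8 ratio, age group, sex at birth, baseline microbiota, and participation in the biopsy sub-study. The method sentence reads: "Subgroup comparisons will use interaction terms in regression models or stratified analyses to explore differential responses to FMT vs. placebo".

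Two cautions follow. The same section says: "These analyses are hypothesis-generating and will be interpreted with caution due to limited power". Statistical considerations labels all additional analyses exploratory, says results will be read in light of the small sample and multiple comparisons, and adds that "no formal correction for multiplicity will be applied in these exploratory analyses".

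The 5% two-sided level is set under Secondary outcome analysis. Further detail on subgroup analyses is referred to a separate SAP, which is not at hand.

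**The concern.** The stated question concerns a difference between effects, so its null hypothesis is that the FMT-versus-placebo effect is the same in each stratum. An interaction term estimates that difference directly. A stratified analysis on its own estimates the effect in each stratum and, if tested, asks whether each is zero. That is a different null hypothesis.

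Because the two methods are joined by *or*, either alone satisfies the protocol. A report could describe FMT as working in one stratum and not the other without an estimate, interval or test for the contrast being described. Splitting 20 people makes such a pattern common even when the effect is uniform. The subgroup paragraph's caution about power warns of differences that may be missed. The risk here is a difference that is not real.

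**Working it through.** **Inputs from the protocol article**
- 10 participants per arm (Sample size {14}).
- Two-sided α = 0.05 (Secondary outcome analysis).
- REG3α: "the difference in REG3α levels between ART-treated (2441 ± 630 pg/mL) and HIV-negative controls (715 ± 243 pg/mL"), a difference of 2441 − 715 = 1726 pg/mL (Sample size {14}).

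**Assumptions**
- Stratum sizes are not given. An even two-way split gives 5 FMT and 5 placebo per stratum.
- Normal outcomes, equal variances, and the same true effect d (in SD units) in both strata.
- The SD of REG3α change is not given. The SDs of levels are used only to place the planned effect on the d scale.

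**Step 1. The plan's own figure.** The protocol says "a sample size of 5 participants per group would allow 80% power to observe an effect". With SD 630, d = 1726/630 = 2.74. With pooled SD √((630² + 243²)/2) = 477.5, d = 3.61. A two-sample t test reaches at least 80% power with 4 per group (89%, SD 630) or 3 per group (90%, pooled SD). At 5 per group, power is 96% or above 99%. The stated 5 is therefore conservative and is not in dispute.

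**Step 2. Power within a stratum.** With n = 5 per arm, the t test has 8 df and noncentrality d·√(5/2). Call its two-sided power p.

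**Step 3. Chance of a split result.** The strata are independent, so P(exactly one significant) = p(1 − p) + (1 − p)p = 2p(1 − p).

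| True d, same in both strata | Power, all 20 | p per stratum | Exactly one stratum significant |
|---|---|---|---|
| 0 | 5% | 0.050 | 9.5% |
| 0.5 | 18.5% | 0.108 | 19% |
| 1.0 | 56% | 0.286 | 41% |
| 1.32 | 80% | 0.454 | 50% |
| 1.37 (half the planned difference: 863/630) | 83% | 0.478 | 50% |
| 1.5 | 89% | 0.549 | 50% |
| 1.81 (half the planned difference: 863/477.5) | 97% | 0.707 | 41% |
| 2.0 | 99% | 0.790 | 33% |
| 2.74 (full planned difference: 1726/630) | >99% | 0.965 | 7% |

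For example, at d = 1.0: 2 × 0.286 × 0.714 = 0.41.

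**Step 4. The interaction test on the same data.** In 100,000 simulated trials per effect size (two strata of 5 + 5, pooled variance, 16 df), the treatment-by-stratum test rejected in 5.0% at d = 0, 5.0% at d = 1.32 and 4.8% at d = 1.41. The share with exactly one significant stratum in those simulations was 9.5%, 49.6% and 50.1%, which agrees with the formula.

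**Step 5. Uneven strata.** With unequal powers p₁ and p₂, the chance is p₁(1 − p₂) + p₂(1 − p₁). Its maximum over d is 52% for 6 versus 4 per arm, 60% for 7 versus 3, and 76% for 8 versus 2. One half is the ceiling only when the two strata have equal power.

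**The case against.** The strongest reply is that the protocol states no rule of the kind modelled above. It does not mention p values within strata, or reading significant-versus-not as a difference. Stratified analysis can equally mean stratum estimates with intervals set side by side, and that has no such error rate. This stands: the percentages are conditional on a reading the protocol permits but does not prescribe.

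A second reply is that subgroup detail belongs to the SAP, which is not shown. The SAP may well settle the matter. Still, the point rests on a choice the protocol itself makes: an SAP using stratified analysis alone would comply with it.

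Third, the cautions go beyond power, since Statistical considerations also mentions multiple comparisons, which is a warning about false positives. That is true and lowers the severity. It does not cover this problem fully, because the inflation arises with a single factor.

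Two stronger readings are tempting and unsupported. A reader might infer that spurious subgroup signals would decide who enters the next trial. The Abstract and Sample size {14} say only that the pilot will inform sample size and power calculations. A reader might also take one half as the typical or maximum error. It is neither: the rate runs from about 10% at no effect to 7% at the full planned effect, peaks in between, and can exceed one half with uneven strata.

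**Conclusion.** The point holds as a minor one. The aim is a comparison of effects between strata, and the protocol permits a method that does not estimate that comparison.

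If within-stratum significance were compared, a uniform effect would look like a differential response in about 10% to 50% of trials for effects from zero to 1.5 SD, falling to 33% at 2.0 SD and 7% at 2.74 SD. The interaction test gives 5% throughout. These figures rest on an even split, normal data with equal variances, and a comparison rule the protocol does not state. Effects near the peak are plausible: the sample size was doubled because full engraftment is not expected, and half the planned difference gives 41% to 50%, depending on the SD.

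No primary or secondary analysis is affected, and the subgroup work is openly hypothesis-generating.

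**What to change.** In Subgroup analyses, replace the choice between the two methods with wording such as: *Any statement on differential response to FMT will rest only on the treatment-by-subgroup interaction estimate with its 95% CI. Stratum-specific estimates with 95% CIs will be shown descriptively, without p values.* Carry the same rule into the SAP, which is to be finalized before database lock. The article reports data collection still in progress, so there is time.

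The change needs no new data and only a sentence or two of text. The downside is wide intervals. With 5 per arm per stratum, the half-width of the interaction CI is about t₀.₉₇₅,₁₆ × √(4/5) = 2.12 × 0.894 = 1.9 SD. Few or no subgroup differences would be claimed, which is what 20 participants can support.

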#### Adjusted analyses

If relevant baseline imbalances are observed between the intervention groups, adjusted analyses may be conducted using multivariable linear or logistic regression models to control for potential confounders (e.g., age, baseline inflammatory marker levels, ART regimen duration).

#### Statistical considerations

All additional analyses will be clearly labeled as exploratory. Results will be interpreted in the context of the small sample size and multiple comparisons and no formal correction for multiplicity will be applied in these exploratory analyses.

### Methods in analysis to handle protocol non-adherence and any statistical methods to handle missing data {20c}

#### Analysis populations

Intent-to-treat (ITT) population: All randomized participants will be included in the primary and secondary outcome analyses according to their originally assigned intervention group, regardless of adherence or protocol deviations. This approach preserves the benefits of randomization and reflects real-world effectiveness.Per-protocol (PP) population: A secondary analysis will be conducted including only those participants who received both doses of the assigned intervention and completed the study without major protocol deviations. This will help assess the efficacy of the intervention under ideal conditions.

#### Handling protocol non-adherence

Participants who discontinue the intervention early or deviate from the protocol (e.g., missed doses, skipped visits) will still be followed for outcome data collection when possible. These participants will remain in the ITT analysis. Sensitivity analyses may compare results from ITT and PP populations to assess the robustness of findings.

#### Handling missing data

Descriptive analysis: The extent, reasons, and patterns of missing data will be summarized.Imputation strategies:oIf missing data are minimal and assumed to be missing completely at random (MCAR), a complete-case analysis may be performed.oIf appropriate, multiple imputations will be used to address missing data under the assumption of missing at random (MAR). Imputation models will include treatment group, baseline values, and other relevant covariates.oFor repeated measures, mixed-effects models will be used, which can accommodate some missing data under the MAR assumption without imputation.Sensitivity analyses: Additional sensitivity analyses may be performed to assess the impact of different assumptions about missingness (e.g., best-case/worst-case scenarios).

All methods used for handling missing data will be described in detail in the SAP.

### Plans to give access to the full protocol, participant-level data, and statistical code {31c}

There are no plans to publicly share the full protocol, participant-level dataset, or statistical code except in the present publication. Access to these materials may be considered on a case-by-case basis upon request, in accordance with institutional policies, participant confidentiality agreements, and applicable regulatory and ethical guidelines. Requests should be directed to the sponsor investigator, [name], and will require appropriate data use agreements and REB approval.

## Oversight and monitoring

### Composition of the coordinating center and trial steering committee {5d}

#### Coordinating center

The trial is coordinated by the Chronic Viral Illness Service (CVIS) at the McGill University Health Centre (MUHC), Glen site, in Montreal, QC, under the supervision of the sponsor investigator, [name]. The coordinating center is responsible for day-to-day operations of the trial, including participant recruitment, data collection, protocol adherence, and communication with collaborating institutions.

#### Trial management team

A dedicated study team, including research coordinators, laboratory leads, and clinicians from both the MUHC and St. Joseph’s Health Care London, provides day-to-day support. This team is responsible for monitoring participant progress, managing data and sample logistics, coordinating study visits, and ensuring compliance with the protocol. The team meets as needed to address operational issues.

#### Trial steering committee (TSC)

The Gutsy study is overseen by a trial steering committee composed of key investigators, as well as representatives from CIHR/CTN. The TSC is composed of the PI, CTN project manager, CTN regulator affair specialist, CTN data manager, CTN statistician, study manager, clinical research coordinator, study nurse, and an external monitor. The TSC provides overall guidance and ensures the study remains aligned with its objectives, ethical standards, and regulatory compliance. The TSC is expected to meet quarterly throughout the trial, or more frequently if necessary.

#### Other committees

Data management and laboratory operations are handled by the MUHC Research Institute and collaborating research laboratories in London, ON. These teams are responsible for sample processing, secure data storage, and maintaining data quality standards.

### Composition of the data monitoring committee, its role and reporting structure {21a}

An independent Data Safety Monitoring Committee (DSMC) has been established to oversee participant safety and monitor trial data throughout the study. The DSMC is composed of independent experts in clinical trials, HIV research, and biostatistics, who are not involved in the conduct of the trial and have no competing interests with the sponsor investigator or funding bodies.

#### Role and responsibilities

The DSMC is responsible for periodic review of cumulative safety data and adverse events, advising on study continuation, modification, or early termination based on emerging safety concerns and ensuring that the rights and well-being of participants are protected.

#### Reporting structure

The DSMC will provide written recommendations to the sponsor investigator after each review meeting. These recommendations will also be communicated to the study team and the REB, as appropriate. The DSMC operates independently from the trial steering committee and sponsor.

#### Meetings and charter

The DSMC meets at regular intervals (e.g., every 6 months) or ad hoc if triggered by a safety event.

### Adverse event reporting and harms {22}

The study follows International Conference on Harmonisation Good Clinical Practice (ICH-GCP) guidelines for the collection, assessment, and reporting of adverse events (AEs).

#### Collection and assessment

Both solicited and spontaneously reported AEs are collected at each study visit. AEs are assessed for intensity (mild, moderate, or severe), causality (relationship to the study intervention), and expectedness. These assessments are recorded in the eCRF.

#### Serious adverse events (SAEs)

SAEs are defined per ICH guidelines and include events that are life-threatening, require hospitalization, result in disability, or death. All SAEs will be reported within 24 h to the medical monitor and sponsor investigator. Additional reporting to the REB will follow institutional and regulatory timelines.

#### Reporting and oversight

All AEs and SAEs will be monitored until resolution or stabilization. Pregnancy, if it occurs during the study, will be reported and followed to outcome. Unanticipated problems involving risk to participants will be reported promptly.

#### Data monitoring committee (DSMC)

The DSMC will review cumulative safety data at pre-specified intervals and make recommendations regarding trial continuation or modification.

### Frequency and plans for auditing trial conduct {23}

Periodic audits may be conducted to ensure compliance with the protocol, Good Clinical Practice (GCP) guidelines, and applicable Health Canada and institutional regulations. These audits are independent of the sponsor investigator and site investigators.

#### Auditing procedures and scope

Audits may be carried out by the CIHR Canadian HIV Trials Network (CTN), institutional quality assurance offices, or regulatory authorities. The audits may involve review of informed consent documentation, verification of source data and eCRF entries, assessment of adherence to inclusion/exclusion criteria, evaluation of adverse event reporting and safety documentation, inspection of investigational product storage, and accountability.

#### Frequency

Audits are anticipated at least once during the study, with additional visits conducted if required based on risk (e.g., protocol deviations, safety signals, or data irregularities).

#### Independence and corrective actions

Auditors will operate independently from the sponsor investigator and site staff. Findings will be documented and reported to the sponsor investigator and trial team. Any corrective actions required will be implemented and tracked in accordance with standard operating procedures.

### Plans for communicating important protocol amendments to relevant parties (e.g., trial participants, ethical committees) {25}

#### Prior ethics and sponsor approval required

No changes will be made to the protocol without prior approval from the Research Ethics Board (REB) and the sponsor investigator, except in cases where the change is necessary to eliminate an immediate hazard to participants.

#### Prompt reporting of changes and unanticipated problems

The investigator agrees to promptly report any changes in the research activity and all unanticipated problems involving risks to human participants or others to the applicable REBs.

#### Documentation of deviations

Any protocol deviations must be documented in the eCRF and reported accordingly.

#### Re-consent of participants

When amendments involve changes that affect participant safety or rights, the protocol implies that participants will be re-consented using an updated informed consent form, although this is standard practice even if not explicitly detailed in the text.

#### Investigators’ responsibilities

Investigators are responsible for adhering strictly to the protocol and for ensuring that any modifications are communicated to the entire study team and implemented only after appropriate approvals.

#### Trial registry and publication updates

adherence to ICH-GCP and Health Canada regulations, which require that trial registries (e.g., ClinicalTrials.gov) and, where applicable, journals and regulators be updated with significant amendments.

### Dissemination plans {31a}

#### Communication with participants

The study’s results will be published in open-access publication. All participants will be given access to the study findings. After study completion, participants will be informed of the overall trial results in study publications, press release, and study results presentations in local meetings.

#### Communication with the scientific and medical community

Results will be published in open-access peer-reviewed journals and presented at scientific conferences, irrespective of the outcome, including those related to HIV research (e.g., CTN semi-annual meetings).

